## Abstract

**Background:**

Excessive postoperative antibiotic use in pediatric surgical patients contributes to antibiotic resistance and increases the risk of *Clostridioides difficile* infection. Despite established guidelines recommending limited postoperative antibiotic duration, many hospitals struggle with de-implementation. This study aims to disseminate and evaluate the impact of a combined strategy to reduce unnecessary postoperative antibiotic use which combines enhanced antimicrobial stewardship program facilitation, defined as a set of actions to enable implementation, combined with order set review and modification. This multi-center study builds on an initial stepped wedge cluster randomized trial involving nine children’s hospitals, where facilitation training improved implementation of surgical prophylaxis guidelines and improved post-operative antibiotic use.

**Methods:**

The current study expands the strategy to a diverse set of hospitals caring for children in the US. Antimicrobial stewardship teams and surgeons from any hospital providing pediatric surgical care will be eligible to participate in facilitation training either as a single session webinar or as asynchronous modules. Based on the integrated Promoting Action on Research Implementation in Health Services (iPARiHS), the facilitation training includes didactic presentations and activities that focus on current evidence related to surgical prophylaxis, evaluation of context, interpersonal relationships, and structured processes to foster change. We will use a quasi-experimental time-series design collecting data from clinicians using a structured interview guide every six months on implementation of prophylaxis guideline congruent order sets as the primary implementation outcome. We will also evaluate trends in at least 20 hospitals collecting quality improvement data through the National Surgical Quality Improvement Program-Pediatrics (NSQIP-P) on postoperative antibiotic use, surgical site infections, and *Clostridioides difficile* infections from 2022–2027.

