Antimicrobial stewardship programs (ASPs), typically co-led by pharmacists and infectious diseases physicians, are a condition of participation by the Centers for Medicare & Medicaid Services. These programs play a crucial role in optimizing antimicrobial selection and duration, reducing the development of AMR, and improving patient safety. ASP team members are well-positioned to integrate evidence-based guidelines, as they collaborate with various clinical services (e.g., surgeons, hospitalists) to ensure appropriate antimicrobial selection, dosing, and duration for both treatment and prophylaxis. However, reducing unnecessary antibiotic use among surgeons remains challenging due to multiple barriers, including skepticism toward evidence, a desire to balance risk of surgical site infection (SSI) with the risk of excessive antibiotic use, entrenched prescribing habits, and limited rapport with ASP teams [12]. Bridging this gap is essential to fostering collaboration, enhancing guideline adherence, and ultimately improving the judicious use of antimicrobials in surgical care [13].

Facilitation is an evidence-based strategy that addresses contextual barriers to change, and allows for the communication of evidence effectively, and builds relationships with end users. This approach has been successful in bridging the relational gap and fostering collaboration between ASP teams and surgeons [14–16]. Our recent study (Operatic 1.0), using a stepped-wedge cluster randomized research design across nine U.S. children’s hospitals, trialed a baseline training with ASP teams focused on reviewing and modifying surgical order sets alone compared to order set modification supplemented with a facilitation training. Our results demonstrated the benefit of ASP teams attending a facilitation workshop to support modifications to electronic order sets over and above order set training alone, ultimately reducing unnecessary postoperative antibiotic use [16–18]. Expanding this combined strategy to a larger network of hospitals and ASP teams has the potential to further improve antibiotic prescribing practices for pediatric surgical patients and contribute to the growing evidence on the effectiveness of facilitation in de-implementing unnecessary healthcare practices.

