### Study setting and participants

This study will be conducted at a minimum of 20 children's hospitals and will recruit from either members of the SHaring Antimicrobial Reports for Pediatric Stewardship (SHARPS) Collaborative [20, 21] or the National Surgical Quality Improvement Program-Pediatric (NSQIP-P) [22, 23]. Founded in 2013, SHARPS aims to improve antimicrobial use across healthcare settings and includes over 70 hospitals with dedicated antimicrobial stewardship teams [20]. NSQIP-P, with 156 participating hospitals, collects data on surgical procedures, including prophylactic antibiotic administration, to enhance pediatric surgical care [22]. ASP teams and surgeon champions from 20 hospitals will be recruited to participate in the updated facilitation workshop via live webinar or asynchronous online at least version. Recruitment will be facilitated through the SHARPS Collaborative Listserv and NSQIP-P webinars, which reach over 150 hospitals. Primary participants will be ASP team members, with extended eligibility for infectious diseases fellows, NSQIP-P surgical leads, surgical clinicians, and surgical fellows.

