### Data collection

Assessing how facilitation supports the integration of surgical prophylaxis guidelines is key to measuring our workshop’s impact. To do so, we will track proximal implementation outcomes (acceptability, reach, and reaction) after training, as well as distal outcomes (e.g., order set changes, facilitation techniques) at 6, 12, and 18 months for all hospitals that participate in the training. For a minimum of 20 hospitals participating in NISQIP-P, we will evaluate key outcomes over time using a quasi-experimental time-series design, comparing three years pre- (2022–2024) and post-intervention (2025–2027). This approach balances internal validity with real-world feasibility and allows for detecting meaningful clinical effects.

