### Clinical outcomes

#### Primary hypothesis

We hypothesize that the appropriately lagged post-intervention percentage of cases receiving unnecessary postoperative antibiotic prophylaxis will be significantly lower than in the pre-intervention period. To test this hypothesis, we will use an intention-to-treat approach for the primary analysis, including all complete case patient data from the NSQIP-P analysis set. A mixed-effects logistic interrupted time series (ITS) regression model will assess the impact of "order set change resulting in reduction" (1) versus "no order set change" (0) on prophylaxis prescriptions. The model will include the intervention (pre vs. post), time (in months), and an interaction term between time and intervention, including a random intercept to account for intra-hospital correlation in the model. The post-intervention slope (β_2) will be the primary estimate of interest (Fig. 2), but we will also investigate differences at 12, 24 and 36 months. The interruption point will be 12 months after each hospital’s first training, with sensitivity analyses at lags 9, 15, and 18 months as well. We will extend the model to adjust for age, surgical subspecialty, procedure type, hospitalization duration, and co-morbidities using Akaike information criterion (AIC)-based variable selection. Subgroup analyses by procedure type and hospital will also be conducted.

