## Discussion

This study aims to disseminate and evaluate the impact of enhanced antimicrobial stewardship program facilitation training, combined with order set review and modification, as de-implementation strategies to reduce postoperative antibiotic use in pediatric surgical patients. Our facilitation strategy proved effective in an initial trial involving nine children's hospitals in the United States as ASP teams successfully modified order sets, implemented surgical prophylaxis guidelines, and improved post-operative antibiotic use [16–18]. The current study will refine our strategy based on feedback and lessons learned from the earlier trial, scaling it up to more than 20 children's hospitals within the NSQIP-P and SHARPS Collaborative networks. If successful, our strategies will help reduce excessive antibiotic use, lower the incidence of CDI, and preserve the efficacy of antibiotic treatments for the future.

Our facilitation workshop introduces a novel approach to reducing inappropriate antibiotic use. Multiple systematic reviews of ASPs indicate that most hospital-based strategies for improving antibiotic use do not emphasize collaboration between ASPs and other specialties [38–40]. In contrast, antimicrobial stewardship professionals who participated in our training reported valuable benefits from the program’s focus on “soft skills”, such as communication techniques aimed at fostering collaboration and rapport [16]. Facilitation, as an implementation strategy, has been shown in other studies to support the development of these skills [14, 16, 41, 42]. By providing this workshop training to ASPs, surgeons, and other clinicians involved in reducing postoperative antibiotic use, we anticipate additional benefits, equipping participants with skills applicable across various specialties to de-implement unnecessary antimicrobial prescribing and use.

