Although implementation science has gained significant traction, substantial gaps remain in the dissemination of evidence-based interventions and strategies [43–45]. Research on the mechanisms and outcomes of implementation strategies in healthcare has often not included dissemination strategies [46], resulting in a limited evidence base to guide effective dissemination efforts. Consequently, dissemination remains an underexplored area and is rarely evaluated through empirical studies [40, 44, 45]. The primary goal of our study is to widely disseminate our facilitation strategy to a broader audience to de-implement unnecessary post-operative antibiotic use at children's hospitals. We will use several approaches to achieve this. First, we will leverage established networks (SHARPS Collaborative and NSQIP-P) to expand the reach of our facilitation strategy. Second, we will engage former participants of our Operatic 1.0 training as facilitators, fostering a continuous exchange of knowledge and best practices. Third, we will incentivize participation by offering CME credits to workshop participants. Lastly, by incorporating both synchronous and asynchronous approaches, we aim to enhance accessibility and engagement across different locations.

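### Nothing keeps the nine hospitals trained in the earlier trial out of the 20-hospital clinical analysis, and any that join would have no untreated baseline

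*Protocol article*

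**What the plan says.** **Who may enter.** The Abstract (Methods) states: "Antimicrobial stewardship teams and surgeons from any hospital providing pediatric surgical care will be eligible to participate in facilitation training". Study setting and participants says the study "will recruit from either members of the SHaring Antimicrobial Reports for Pediatric Stewardship (SHARPS) Collaborative" or of NSQIP-P, which has 156 hospitals. Workshop content and delivery adds that completing the training lets a site contribute to data collection. Data collection sets the clinical evaluation at a minimum of 20 NSQIP-P hospitals, with 2022–2024 as the period before and 2025–2027 as the period after.

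**What is analysed.** Under Primary hypothesis, all complete cases in the NSQIP-P analysis set enter a mixed-effects logistic interrupted time series with a random hospital intercept. Exposure is coded 1 for an order set change that led to a reduction and 0 for no change. The post-intervention slope is the primary estimate. On timing: "The interruption point will be 12 months after each" hospital's first training. The listed adjustment variables include no term for earlier training.

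**What is said of the earlier trial.** Background describes it as "using a stepped-wedge cluster randomized research design across nine U.S. children’s hospitals" and reports: "Our results demonstrated the benefit of ASP teams attending a facilitation workshop to support modifications to electronic order sets". The Discussion says: "Our facilitation strategy proved effective in an initial trial involving nine children's hospitals in the United States". It also says that "we will engage former participants of our Operatic 1.0 training as facilitators".

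**The concern.** The design compares each hospital with its own past, so it rests on that past being free of the strategy under test. A hospital trained in the earlier trial does not meet this condition. Three things are at stake if such hospitals enter the primary set:

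- **Contrast.** Their remaining scope for improvement is probably smaller, which pulls the average pre/post difference towards zero.
- **Slope.** If prescribing in such a hospital is still falling after the earlier training, the fall runs through the break and becomes part of the post-intervention trend.
- **Exposure coding.** A hospital that shortened its order sets during the earlier trial and has nothing left to change would be coded as having no order set change, although it has been treated.

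The time origin also needs a definition. For an earlier-trial hospital, the first training taken literally is the earlier one, which does not fit the 2022–2024 / 2025–2027 split.

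**Working it through.** **Step 1: do the stated rules let these hospitals in?** Training is open to any hospital with pediatric surgical care. Trained sites may contribute data, the clinical set is NSQIP-P hospitals, and all complete cases are analysed. No link in this chain removes an earlier-trial hospital that belongs to NSQIP-P. The number that will do so (k) is not given. The size of the earlier trial bounds it at 0 to 9.

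**Step 2: is their baseline untreated?** The article reports the earlier trial as finished and effective, and the new post period starts in 2025. Training there therefore came before or during 2022–2024. The dates are not given, and they matter: training well before 2022 with a stable result is less harmful than training within 2022–2024.

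**Step 3: direction for the slope.** Suppose an earlier-trial hospital declines at the same rate before and after the new break, so that the new workshop adds nothing. The trend after the break is still downward and would be credited to the workshop if that trend is the estimate, as the Fig. 2 caption describes it. The change in slope would be zero, which pulls a pooled change towards no effect. The sign of the bias therefore depends on which quantity is reported.

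**Step 4: the plan's own power figure.** Power and sample size calculations gives 20 hospitals, 10 steps, 14 procedures per hospital per month, ICC 0.12, a 45% baseline, a difference of at least 5% (read here as 45% to 40%), two-sided 5% and at least 80% power. The mean binomial variance is (0.45 × 0.55 + 0.40 × 0.60)/2 = 0.24375. With the Hussey and Hughes stepped-wedge variance and categorical period effects:

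- 11 one-month periods: SE 0.0286, power 41.5%.
- 60 monthly periods: SE 0.0225, so 0.05/0.0225 − 1.960 = 0.262 and power is about 60%.
- 60 months pooled into 11 periods: SE 0.01245, power 98.0%; with cluster autocorrelation 0.9, 80.6%.

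The article does not fix period length, time adjustment or autocorrelation, so its figure cannot be uniquely reproduced. It can be reached under some readings and is not disputed here. The illustration below starts from exactly 80%.

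**Step 5: dilution of the pre/post difference.** Let r be the share of the effect still attainable in an already-trained hospital (an assumption). Then

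D = 5 × (1 − k(1 − r)/20) points

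power = Φ((1.960 + 0.842) × D/5 − 1.960)

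Example with k = 5 and r = 0: D = 5 × 15/20 = 3.75. Then 2.802 × 0.75 − 1.960 = 0.141, and Φ(0.141) = 0.556.

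| k | D, r = 0 | Power | D, r = 0.5 | Power |
|---|---|---|---|---|
| 0 | 5.00 | 80% | 5.00 | 80% |
| 1 | 4.75 | 76% | 4.875 | 78% |
| 3 | 4.25 | 66% | 4.625 | 74% |
| 5 | 3.75 | 56% | 4.375 | 69% |
| 9 | 2.75 | 34% | 3.875 | 58% |

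The table keeps the standard error fixed and spreads the already-trained hospitals evenly over the roll-out. It concerns the pre/post difference used for the power calculation, not the slope.

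**The case against.** The strongest reply is that this is silence in a condensed article. No sentence places an earlier-trial hospital among the 20, and the language of expansion and scaling up suggests new sites. The open eligibility sentence governs workshop attendance, whereas the clinical set is narrower. The random intercept absorbs a lower but stable starting level. Read with the stated calendar periods, first training most naturally means training in this study. The hospital survey asks about stewardship efforts on post-operative antibiotics, and subgroup analyses by hospital are planned, so affected sites could be identified.

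Much of this stands. It limits the size of the problem and makes it conditional. It does not remove it: the entry and analysis rules are stated, and followed as written they admit these hospitals to the primary model. A random intercept deals with level. It does not deal with a continuing trend, reduced scope for gain or the exposure coding. Identifying sites by survey is not a rule for analysing them.

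Three stronger readings are tempting and should be resisted:

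- **That the effect is in fact diluted.** This needs k above zero and a reduced remaining gain, and the article gives neither.
- **That the return of former participants shows their hospitals will supply outcome data.** They return as facilitators, and nothing more is said.
- **That the plan's power drops to one particular figure.** The starting power depends on choices that the article does not state. A hospital may also have gain left, because sites in the earlier trial targeted different procedures.

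**Conclusion.** The point holds as a conditional one. The article does not keep earlier-trial hospitals out of the primary clinical analysis and does not adjust for earlier training. Any that join lack an untreated baseline. The likely result is dilution of the pre/post contrast, bias of uncertain sign in the post-intervention slope, and misclassified exposure where order sets had already been changed. The size ranges from no loss (k = 0) to an average effect of 2.75 points and about 34% power (k = 9, no remaining gain, 80% at the start). With half the gain left, the k = 9 figure is about 58%. Both k and the remaining gain are assumptions. This is a cheap improvement and not a reason to doubt the design as a whole.

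**What to change.** Under Primary hypothesis, state that hospitals trained in the earlier trial may attend the workshop but are left out of the primary clinical analysis set. At minimum, pre-specify a sensitivity analysis without them. In the same place, define first training as a hospital's first training in the present study.

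The cost is one or two sentences. The downside is that a few willing sites leave the primary set: at most nine of 156 NSQIP-P hospitals, which leaves at least 156 − 9 = 147 from which to recruit 20.

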**Discussion:**

By scaling up this intervention, the study aims to provide a robust evaluation of its effectiveness across diverse hospital settings. If successful, this approach could inform future antimicrobial stewardship efforts in pediatric and adult surgical populations, offering a scalable model for reducing inappropriate antibiotic use while maintaining patient safety.

**Supplementary Information:**

The online version contains supplementary material available at 10.1186/s13012-025-01460-5.

Contributions to the literature
This study advances de-implementation research by evaluating facilitation combined with order set modifications as a scalable strategy to reduce unnecessary postoperative antibiotic use in pediatric surgery, addressing a critical gap in antimicrobial stewardship.Unlike traditional antimicrobial stewardship interventions, this approach emphasizes theory-based interdisciplinary facilitation training to strengthen collaboration between stewardship teams and surgical departments.With a multi-center study design spanning more than 20 hospitals, this study enhances the generalizability of de-implementation strategies and evaluates long-term outcomes using time-series analysis.The study contributes to ‘dissemination science’ by examining how asynchronous training and targeted facilitation can support the spread and adoption of evidence-based prescribing practices.

## Background

Antimicrobial-resistant (AMR) infections, driven by excessive and inappropriate antibiotic use, are an increasing public health emergency. A dramatic increase in the carriage of multidrug-resistant organisms has been observed since 2000 with projections indicating that if no efforts are made to improve antimicrobial use, AMR infections could result in 10 million deaths annually by 2050, surpassing the annual number of deaths due to cancer (8 million) [1–4]. *Clostridioides difficile* infection (CDI) is an adverse event associated with antibiotic use and is a more direct and immediate harmful outcome. Hospitalized children who develop CDI face an increased risk of death, prolonged hospitalization by up to seven days, and additional hospital costs of approximately $100,000 [5].

Even a single dose of perioperative antibiotic prophylaxis increases the risk six-fold for CDI [6, 7]. Studies indicate that inappropriate pre- and post-operative antibiotic prophylaxis occurs in up to 56% of cases, with unnecessary postoperative doses administered in 55% of low-risk procedures (clean and clean-contaminated cases) [6, 8, 9]. Improving the use of surgical antibiotic prophylaxis in the postoperative period across children’s hospitals presents a significant opportunity to reduce inappropriate antibiotic overuse. In published guidelines from the Centers for Disease Control and Prevention and the American Academy of Pediatrics Committee on Infectious Diseases, both strongly recommend limiting surgical antibiotic prophylaxis to a single perioperative dose for clean and clean-contaminated cases [10]. Furthermore, they advise discontinuing prophylaxis once the surgical incision is closed for uncomplicated procedures [11].

Antimicrobial stewardship programs (ASPs), typically co-led by pharmacists and infectious diseases physicians, are a condition of participation by the Centers for Medicare & Medicaid Services. These programs play a crucial role in optimizing antimicrobial selection and duration, reducing the development of AMR, and improving patient safety. ASP team members are well-positioned to integrate evidence-based guidelines, as they collaborate with various clinical services (e.g., surgeons, hospitalists) to ensure appropriate antimicrobial selection, dosing, and duration for both treatment and prophylaxis. However, reducing unnecessary antibiotic use among surgeons remains challenging due to multiple barriers, including skepticism toward evidence, a desire to balance risk of surgical site infection (SSI) with the risk of excessive antibiotic use, entrenched prescribing habits, and limited rapport with ASP teams [12]. Bridging this gap is essential to fostering collaboration, enhancing guideline adherence, and ultimately improving the judicious use of antimicrobials in surgical care [13].

Facilitation is an evidence-based strategy that addresses contextual barriers to change, and allows for the communication of evidence effectively, and builds relationships with end users. This approach has been successful in bridging the relational gap and fostering collaboration between ASP teams and surgeons [14–16]. Our recent study (Operatic 1.0), using a stepped-wedge cluster randomized research design across nine U.S. children’s hospitals, trialed a baseline training with ASP teams focused on reviewing and modifying surgical order sets alone compared to order set modification supplemented with a facilitation training. Our results demonstrated the benefit of ASP teams attending a facilitation workshop to support modifications to electronic order sets over and above order set training alone, ultimately reducing unnecessary postoperative antibiotic use [16–18]. Expanding this combined strategy to a larger network of hospitals and ASP teams has the potential to further improve antibiotic prescribing practices for pediatric surgical patients and contribute to the growing evidence on the effectiveness of facilitation in de-implementing unnecessary healthcare practices.

The overall goal of the proposed study is to widely disseminate our facilitation workshop as a strategy to de-implement unnecessary post-operative antibiotics in children. To achieve this, we will: (1) update and adapt our facilitation workshop to make it accessible to over 150 children's hospitals in the United States, (2) evaluate implementation outcomes related to the workshop, assessing how the skills and knowledge gained impact the adoption of prescribing guidelines, reach through order set changes, and the application of facilitation techniques, and (3) evaluate the clinical impacts, including reductions in inappropriate antibiotic use and potential effects on surgical site infections and CDI across 20 hospitals. By the end of the dissemination project, we conservatively estimate that our efforts will impact approximately 50,000 surgical cases during the project period.

